# Assessing the efficacy and safety of mycophenolate mofetil versus azathioprine in patients with autoimmune hepatitis (CAMARO trial): study protocol for a randomised controlled trial

**DOI:** 10.1186/s13063-022-06890-w

**Published:** 2022-12-13

**Keywords:** Autoimmune hepatitis, Azathioprine, Mycophenolate mofetil, First-line treatment, Induction therapy, Randomized controlled trial, Remission, Biochemical remission, Phase IV trial

## Abstract

**Background:**

Currently, the standard therapy for autoimmune hepatitis (AIH) consists of a combination of prednisolone and azathioprine. However, 15% of patients are intolerant to azathioprine which necessitates cessation of azathioprine or changes in therapy. In addition, not all patients achieve complete biochemical response (CR). Uncontrolled data indicate that mycophenolate mofetil (MMF) can induce CR in a majority of patients. Better understanding of first-line treatment and robust evidence from randomised clinical trials are needed. The aim of this study was to explore the potential benefits of MMF as compared to azathioprine, both combined with prednisolone, as induction therapy in a randomised controlled trial in patients with treatment-naive AIH.

**Methods:**

CAMARO is a randomised (1:1), open-label, parallel-group, multicentre superiority trial. All patients with AIH are screened for eligibility. Seventy adult patients with AIH from fourteen centres in the Netherlands and Belgium will be randomised to receive MMF or azathioprine. Both treatment arms will start with prednisolone as induction therapy. The primary outcome is biochemical remission, defined as serum levels of alanine aminotransferase and immunoglobulin G below the upper limit of normal. Secondary outcomes include safety and tolerability of MMF and azathioprine, time to remission, changes in Model For End-Stage Liver Disease (MELD)-score, adverse events, and aspects of quality of life. The study period will last for 24 weeks.

**Discussion:**

The CAMARO trial investigates whether treatment with MMF and prednisolone increases the proportion of patients in remission compared with azathioprine and prednisolone as the current standard treatment strategy. In addition, we reflect on the challenges of conducting a randomized trial in rare diseases.

**Trial registration:**

EudraCT 2016-001038-91. Prospectively registered on 18 April 2016.

**Graphical Abstract:**

[figure not shown]

**Supplementary Information:**

The online version contains supplementary material available at 10.1186/s13063-022-06890-w.

## Background

Autoimmune hepatitis (AIH) is a severe chronic liver disease associated with cirrhosis and liver failure [1, 2]. AIH is a rare disease, its prevalence is estimated at 17–23 cases per 100,000 inhabitants in Europe [3, 4]. It is characterised by a spectrum of clinical manifestations and may lead to complications of progressive liver disease, including cirrhosis, portal hypertension, and hepatocellular carcinoma. Untreated AIH has very poor outcomes and is usually fatal [2, 5].

Immunosuppressive therapy consisting of azathioprine and corticosteroids has emerged as the mainstay of active autoimmune hepatitis management. This has greatly improved survival rates [6–8]. Normalisation of transaminases is achieved in 65–70% after 6 months, irrespective of prednisone dosage [9]. However, almost 20% of patients experience adverse effects (AEs) with azathioprine treatment, such as nausea, vomiting, arthralgia, skin rash and fever, which necessitate cessation of treatment in approximately 15% of patients in the first year [10, 11]. In recent years, mycophenolate mofetil (MMF) has been explored as an alternative option to standard care in AIH treatment. Most studies focused on the use of MMF as second-line rescue therapy in AIH patients who were either intolerant or refractory to azathioprine. MMF seems to be generally better tolerated than azathioprine. Several retrospective studies reported remission rates, which varied from 25 to 100% (Table 1) [12–25]. This has led to recommendations in the European Association of the Study of the Liver (EASL) guidelines and the European Society for Paediatric Gastroenterology Hepatology and Nutrition (ESPGHAN) position statement of MMF as second-line treatment for patients who do not respond to or do not tolerate azathioprine [26, 27]. Meanwhile, MMF has aroused interest as an alternative option for AIH induction therapy. A prospective uncontrolled study explored the efficacy of MMF in treatment-naive AIH patients [28]. Fifty-nine treatment-naive AIH patients received open-label MMF at a final dose of 1.5–2 g daily combined with a standardised prednisolone tapering scheme. Eighty-eight per cent of patients had an initial clinical and biochemical response with normalisation of serum aspartate transferase (AST), alanine transferase (ALT) and immunoglobulin gamma (IgG) levels. While the data on MMF in AIH patients are promising, randomised clinical trials are needed to generate high-quality evidence.

**Table 1 Tab1:** Studies of MMF in AIH

Author	Year	Type of study	Patients, ***n***	Population (age group, variant, cirrhosis, indication for MMF)	Biochemical remission	Definition endpoint
**Richardson** [22]	2000	Retrospective	7	Population: adult and children Variant: *n*=0 Cirrhosis: *n*=1 Indication: refractory disease (*n*=4), intolerance AZA (*n*=3)	71%	Normalisation of ALT at 3 months
**Devlin** [24]	2004	Retrospective	5	Population: adult Variant: *n*=0 Cirrhosis: *n*=2 Indication: refractory disease (*n*=3), side-effects (*n*=1), other reasons (*n*=1)	100%	Normalised ALT at any timepoint
**Chatur** [21]	2005	Retrospective	16 (11/16 on MMF monotherapy)	Population: adult Variant: *n*=0 Cirrhosis: unknown^a^ Indication: unknown^a^	64%	Normalisation of serum aminotransferases at any timepoint
**Czaja** [25]	2005	Retrospective	8	Population: adult Variant: *n*=0 Cirrhosis: *n*=1 Indication: treatment naïve (*n*=1), incomplete response (*n*=4), treatment failure (*n*=2), multiple relapses (*n*=1)	0%	Normalisation of AST, bilirubin, and IgG at any timepoint
**Inductivo-Yu** [20]	2007	Retrospective	15	Population: adult Variant: *n*=2 Cirrhosis: *n*=8 Indication: biochemical or histologic non-response (*n*=11), significant side effects (*n*=14)	73%	Normalisation of ALT at unknown time point
**Hlivko** [19]	2008	Retrospective	29	Population: adult Variant: unknown^a^ Cirrhosis: unknown^a^ Indication: intolerance or nonresponse (*n*=12 ➔ 9 prednisone + MMF; 1 MMF alone; 1 prednisone + MMF + tacrolimus; 1 MMF + cyclosporine), first-line therapy (*n*=17)	55%	Resolution of symptoms, reduction in serum aminotransferase levels to <2 ULN, normalisation of serum bilirubin and γ-globulin levels (and improvement in liver histology to normal or only mild portal hepatitis) at unknown time point
**Hennes** [18]^**b**^	2008	Retrospective	36	Population: unknown Variant: unknown Cirrhosis: unknown Indication: side effects (*n*=28), insufficient response (*n*=9), pregnancy (*n*=1)	39%	AST <2x ULN at unknown timepoint
**Wolf** [17]	2009	Retrospective	16	Population: unknown Variant: *n*=4 Cirrhosis: unknown Indication: intolerance (*n*=7), refractory disease (*n*=6), other reasons (*n*=3)	31%	Reduction of ALT from greater than twice normal to less than twice normal
**Baven-Pronk** [15]	2011	Retrospective	45	Population: adult Variant: (*n*=15) Cirrhosis: (*n*=24) Indication: AZA-non-responders (*n*=22), AZA-intolerance (*n*=23)	47%	Normalisation of AST and/or ALT at any timepoint after starting MMF
**Zachou** [28]	2011	Prospective	59	Population: adult + children Variant: *n*=0 Cirrhosis at presentation: *n*=14 Indication: treatment-naïve (*n*=59)	88%	Normalisation of AST, ALT, and γ-globulins within 12 months
**Jothimani** [16]	2014	Retrospective	20	Population: adult Variant: *n*=3 Cirrhosis: *n*=5 Indication: AZA intolerance (*n*=18), refractory disease (*n*=2)	74%	Normalisation of ALT and/or AST at any timepoint
**Zachou** [29]	2016	Prospective	109	Population: adult + children Variant: *n*=0 Cirrhosis at presentation: *n*=26 Indication: treatment-naïve (*n*=109)	72%	Normalisation of ALT, AST, and IgG, symptoms improved or disappeared and liver histology, if performed, showed minimal or no inflammation at 3 months treatment
**Roberts** [14]	2018	Retrospective	105	Population: adult Variant: *n*=0 Cirrhosis: *n*=38 Indication: suboptimal response (*n*=42), treatment intolerance (*n*=63)	60%	Normalisation of ALT, AST, and IgG, with or without normal liver histology within the first 2 years of treatment
**Nicoll** [13]	2019	Retrospective	105	Population: adult Variant: *n*=0 Cirrhosis: *n*=38 Indication: intolerance (*n*=63), nonresponse (*n*=42)	60%	ALT, AST and IgG <ULN, with or without normal liver histology, within the first 2 years of treatment
**Giannakopoulos** [12]	2019	Retrospective	22	Population: adult Variant: *n*=0 Cirrhosis: *n*=6 Indication: intolerance (*n*=14), non-response (*n*=5), intolerance + non-response (*n*=3)	45%	Normalisation of ALT and AST within 3 to 30 weeks
**Liberal** [23]	2021	Retrospective	18	Population: adult Variant: *n*=0 Cirrhosis: *n*=4 Indication: intolerance (*n*=9), refractory disease (*n*=9)	39%	Normalisation of AST, ALT, and IgG at 12 months
**Dalekos** [30]	2021	Prospective	32	Population: adult + children Variant: *n*=0 Cirrhosis: *n*=6 Indication: treatment-naïve (*n*=32)	93.8%^c^	Normalisation of AST, ALT, and IgG at 6, 12 months, and at the end of follow-up

*AIH* autoimmune hepatitis, *ALT* alanine aminotransferase, *AST* aspartate aminotransferase, *AZA* azathioprine, *HAI* Hepatitis Activity Index, *IgG* immunoglobulin G, *ULN* upper limit of normal, *MMF* mycophenolate mofetil

^a^Patients with MMF: no separate baseline data ^b^full text not available ^c^at 6 months

## Methods

### Design and methods

The trial protocol is written in accordance with the Standard protocol items: recommendation for interventional trials (SPIRIT) guidelines [31] (see Table 4 and the Additional file 1: SPIRIT checklist).

### Study aim

The CAMARO trial aims to investigate whether MMF and prednisolone are superior to azathioprine and prednisolone in inducing remission in treatment-naive AIH patients. The hypothesis is that MMF will be more effective than azathioprine in inducing remission, both combined with a standard prednisolone schedule.

### Study design and recruitment

CAMARO is a phase IV, randomised (1:1), open-label, parallel-group, multicentre superiority trial in 70 patients with treatment-naive AIH. All patients with established AIH according to the simplified criteria for the diagnosis of AIH [32] and who are considered for induction therapy will be eligible for the study. Eligibility will be assessed at the screening visit (SV) and patients will start with prednisolone according to the treatment schedules in Tables 2 and 3. A patient may enter the study at any time point in the first 4 weeks, as long as the prednisone schedule has been used for induction therapy. After informed consent, patients will be randomised in a 1:1 ratio to one of the two treatment arms. At 4 weeks, patients will consequently start with either azathioprine or MMF in dosages exactly according to the schedule (Tables 2 and 3). Eight follow-up visits are scheduled at weeks 4, 8, 12, 16, 20, and 24. The week 24 visit is the end of the treatment visit. After that, patients can continue azathioprine or MMF as assigned, as maintenance therapy. A trial flowchart is shown in Fig. 1.

**Table 2 Tab2:** Treatment schedule for patients 40–80 kg

Week	Prednisolone (mg/day)	Azathioprine (mg/day)	MMF (mg/day)
1	40	-	-
2	30	-	-
3	25	-	-
4	20	-	-
5	15	50	1000
6	12,5	50	1000
7[contact]
9+10	7,5	100	2000
From week 11 onwards	5	100	2000

*MMF* mycophenolate mofetil, *mg* milligrams

**Table 3 Tab3:** Treatment schedule for patients >80 kg

Week	Prednisolone (mg/day)	Azathioprine (mg/day)	MMF (mg/day)
1	60	-	-
2	45	-	-
3	30	-	-
4	20	-	-
5	15	50	1000
6	12,5	50	1000
7[contact]
9+10	7,5	100	2000
From week 11 onwards	5	100	2000

*MMF* mycophenolate mofetil, *mg* milligrams

**Fig. 1 Fig1:**
[figure not shown]
Flowchart CAMARO trial. AIH, autoimmune hepatitis; MMF, mycophenolate mofetil

Patients will be selected from outpatient clinics of the participating centres or referred by other centres. This is the predominant way of recruitment. Flyers with a brief introduction to the trial and researchers’ contact information will also be used for recruitment. Physicians can contact the study coordinators via telephone 24 h per day, seven days per week, to check the eligibility criteria. Potential participants will be approached by their treating physician. The study will be explained by the local Principal Investigator (PI) and their team. Potential participants received a Patients Information Form (PIF) and will have the possibility to ask questions. They have at least one week to consider the study. After one week, potential participants will be contacted, and they will get the opportunity to ask questions. The screening evaluation includes disease-related signs and corresponding laboratory tests, including a urine pregnancy test (in women of childbearing age). In some participating centres, informed consent forms will include the option to consent to collect and use biobank blood samples. The blood samples will be drawn at screening and week 24 for future research. The biobank samples will be processed locally and stored in local biobank facility. Additional tests can be performed when new research questions arise during the study. Where possible, backup samples for central endpoint analysis were drawn and stored locally.

### Participants

The objective is to include 70 patients with treatment-naive AIH. The study will be conducted by the Dutch Autoimmune Hepatitis Working Group. Individuals who meet the entry criteria and complete the baseline visit will be enrolled in one of the participating centres. In total, fourteen centres are participating in the trial, including seven Dutch university medical centres. A list of study sites can be obtained at https://clinicaltrials.gov/ct2/show/NCT02900443.

#### Inclusion criteria

The inclusion criteria are:Probable or definite diagnosis of AIH according to the simplified criteria for the diagnosis of Autoimmune Hepatitis [32]:Definite AIH: ≥7Probable AIH: 6First presentation of AIH requiring treatment according to the current EASL guidelines [27]Age ≥18 years

All patients will undergo a liver biopsy since this is a prerequisite for the diagnosis of AIH. The liver biopsy must be scored at least compatible or typical for AIH according to the simplified criteria [32].

#### Exclusion criteria

A potential participant who meets any of the following criteria will be excluded from participation in this study:Variant syndrome with primary sclerosing cholangitis (PSC) or primary biliary cholangitis (PBC) (Paris criteria [33], strong positive AMA, past liver biopsy with characteristic signs of PBC or cholangiographic findings compatible with PSC)Presentation with acute liver failure, defined as presence of hepatic encephalopathy and coagulopathy (international normalised ratio (INR) > 1.5)Current treatment with predniso(lo)ne and/or immunosuppressive medication for an indication other than AIHCurrent systemic infectionOther clinically significant medical conditions that could interfere with the trialIf female of childbearing potential: known pregnancy, or unwilling to practice anticontraceptive measuresHistory of noncompliance with medical regimens, or patients who are considered to be potentially unreliable or unable to participateMental instability or incompetence, such that the validity of informed consent or compliance with the trial is uncertain

### Withdrawal from the study and replacement

Participants can leave the study at any time for any reason if they wish to do so without any consequences. The investigator can decide to withdraw a subject from the study for urgent medical reasons, such as (but not limited to) (a) occurrence of any AE or abnormality in a laboratory assessment which warrants the subject’s discontinuation from the trial, (b) patient noncompliance defined as refusal or inability to adhere to the trial schedule or procedures, (c) at the request of a regulatory authority, (d) the patient becomes pregnant, and (e) or the patients is lost to follow-up. If so, the patient will be followed and data will be recorded in an observational manner. All data generated up to the time of discontinuation from the study will be used for the intention to treat analysis and the reason(s) for discontinuation will be recorded.

Patients who participate in the study, but drop out for the study in the first 4 weeks will be replaced by new patients. If the participant is being withdrawn because of an AE, that AE must be indicated as the reason for withdrawal. Participants who withdraw from the study will be seen for a follow-up 4 weeks later. AEs and concomitant medication will be assessed and blood will be drawn.

### Treatment groups and randomization

All participants, regardless of group allocation, will be treated with prednisolone induction therapy. The prednisolone dosage will commence at 40 mg or 60 mg per day, dependent on weight, and will be tapered according to a fixed schedule (Tables 1 and 2) which is based on the EASL Clinical Practice Guidelines [27]. We aim that all patients will eventually taper down to 5 mg prednisolone daily. Participants will have reduced prednisolone to 20 mg/day at week 4. Participants will be randomised 1:1, with a variable block randomization (block size 4, 6, 8) between azathioprine or MMF, stratified per participating centre for the presence of cirrhosis (yes/no). For randomisation of a patient, physicians can contact the study coordinators via telephone 24 h per day, 7 days per week in order to check the eligibility criteria and to verify whether informed consent has been obtained. Randomisation will be done by the study coordinator using the electronic case report form by Castor Electronic Data Management (Castor EDC). The study is an open-label trial which means that both patients and all research staff (including the primary caregiver and principal investigator) will be aware of the study arm allocated and thus are not blinded. Only outcome assessors will be blinded during the analyses. Therefore, unblinding will not occur in this study. Azathioprine and MMF will be packed and labelled as study medication according to Good Manufacturing Practice (GMP) guidelines by the pharmacy of the Leiden University Medical Center.

#### Intervention group: mycophenolate mofetil (MMF)

Patients in the intervention group will receive oral MMF in a total daily dose of up to 2000 mg, split-dose, in addition to a prednisolone schedule, based on the EASL guidelines [27]. MMF will be started in a dosage of 500 mg, twice daily combined with prednisolone. If there are no problems with tolerability of MMF, patients will be titrated after 2 weeks to 1000 mg twice daily for the rest of the study. In case of MMF-related AEs (e.g. cytopenia), dose reduction can be considered by the treating physician. The dosage will be reduced with 250 mg twice daily until AEs disappear. When AEs persist after dose reduction, MMF can be discontinued. Those patients will be followed-up after discontinuation and will be treated according to standard of care by the treating physician. The teratogenic effect of MMF will be discussed in detail in women of childbearing potential and men who wish to father a child at the screening visit. All female patients of childbearing potential will need to undergo a pregnancy test at screening and will be instructed to take adequate anticontraceptive measures during the study.

#### Control group: azathioprine

The control arm will receive standard of care treatment for AIH according to the recent EASL guidelines [27]. The prednisolone dosage is based on these guidelines and is identical to the intervention group. In addition to prednisolone, standard therapy consists of azathioprine in a dosage of 50 mg daily for the first 2 weeks, and 100 mg daily for the rest of the study. The patients in this group will undergo the same study schedule as the patients in the intervention group. In case of azathioprine intolerance and/or AEs, a dosage reduction is allowed from 100 mg to 50 mg daily. If AEs related to azathioprine persist at a dosage of 50 mg, discontinuation of the drug can be considered. In that case, a patient is will be withdrawn from the study and followed up by standard of care.

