#### Secondary outcomes

The secondary outcomes are to evaluate the efficacy of MMF versus azathioprine in combination with a 24-week prednisolone taper regimen in patients with AIH measured by the following:Biochemical remission at 24 weeks and at anytimeTime to biochemical remissionComplete biochemical response: defined as normalisation of AST, ALT, and IgG at 24 weeksNon-response at 4 weeks: defined as <50% decrease of serum transaminases within 4 weeks after initiation of treatmentInsufficient response: defined as lack of complete biochemical response determined at 24 weeksChanges in MELD score (and its components bilirubin, INR, creatinine), and in albuminChanges in liver stiffness, measured by transient elastographyN-terminal procollagen-III-peptide, Enhanced Liver Fibrosis (ELF) scoreChanges in quality of life measured with Short Form (SF)-36Difference in side-effects, AEs and serious AEs (SAE), based on clinical examination (e.g. hypertension), laboratory assessments (e.g. neutropenia and new-onset diabetes), and patients-reported symptoms between the MMF and azathioprine groupsThe level of ALT, AST, gamma-glutamyl transferase (GGT) in both groupsPercentage of patients with biochemical remissionRatio of ALT to lowest ALT everExtrahepatic AIH manifestations (e.g. arthralgia)Patient survivalFatigue indexPruritis visual analogue scoreDifference in cumulative corticosteroid dose between the MMF and azathioprine groups

Ancillary studies can be performed on blood samples as determined by the Dutch AIH Group steering committee.

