Only high-quality unbiased data coming from RCTs can inform future guidelines. Despite a clear strategy at the outset and taking into account a recruitment rate with a delayed start at the beginning of the trial, recruitment in the CAMARO trial has taken much longer than the initially predicted three years. A number of barriers impeded rapid enrolment. Successful recruitment in clinical trials is known to be one of the most challenging aspects in study completion, especially in the field of rare diseases. First, an international multicentric setup was needed to achieve recruitment targets. Due to various site-specific obstacles, administrative processes were met with delays (e.g. different electronic infrastructure, institutional policies, and contract requirements). Second, the choice of induction therapy is at the discretion of the attending physician. Only patients who were prescribed the fixed-dose prednisolone regimen could be included. This requirement resulted in lower inclusion rates. However, using a fixed-dose schedule instead of symptom-triggered treatment allows better comparison across arms. Third, a current challenge is that industry-driven trials in this field are on the horizon. These projects are better funded and allow for reimbursement of physician-patient interaction. We did not offer reimbursement for the time invested by physicians. In fact, it is remarkable that we have been able to conduct this study despite lacking the necessary funding. The CAMARO is an example of drug repurposing as a strategy to identify new uses for approved or investigational drugs outside the original label's scope. MMF and different second- and third-line therapies (e.g. tacrolimus, ciclosporin) have never been registered for specific use in AIH. Active presence, both onsite and on social media, low-threshold assistance with inclusion, use of newsletters for clinicians, and involvement of patient organisation(s) are of the utmost importance for awareness of a clinical trial. In order to spur enrolment, the option of a phone consultation with the study coordinators by phone (24/7) was given to verify eligibility criteria. This increased the rate of inclusions. Simultaneously, a close-knit international network of general and academic hospitals is fundamental for a successful RCT in rare diseases like AIH. The CAMARO trial is carried out by the Dutch Autoimmune Hepatitis Working Group and fourteen participating centres in the Netherlands and Belgium. Inclusion is reliant on this network.

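### Total corticosteroid dose is a weak between-arm outcome: both arms share one fixed weight-banded schedule, so only off-schedule use carries drug information, and the count may stop earlier on azathioprine

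*Protocol article*

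**What the plan says.** The Secondary outcomes section of the protocol article opens: "The secondary outcomes are to evaluate the efficacy of MMF versus azathioprine in combination with a 24-week prednisolone taper regimen". The last item in its list is the difference between the two groups in cumulative corticosteroid dose.

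The prednisolone itself does not depend on arm:
- Treatment groups and randomization: "The prednisolone dosage will commence at 40 mg or 60 mg per day, dependent on weight", and it "will be tapered according to a fixed schedule".
- Control group: "The prednisolone dosage is based on these guidelines and is identical to the intervention group".
- Study design and recruitment: "At 4 weeks, patients will consequently start with either azathioprine or MMF in dosages exactly according to the schedule". Weeks 1–4 are thus prednisolone alone.
- Discussion, on why the taper is fixed: "using a fixed-dose schedule instead of symptom-triggered treatment allows better comparison across arms".

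The follow-up wording after a study drug is stopped differs by arm. For azathioprine stopped because of persisting adverse events: "In that case, a patient is will be withdrawn from the study and followed up by standard of care". For MMF, the intervention-group section says that stoppers are followed up and treated by standard of care; it does not mention leaving the study. The withdrawal section says that patients withdrawn by the investigator are followed and their data recorded observationally. It also says that data generated up to discontinuation from the study enter the intention-to-treat analysis.

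**The concern.** A cumulative steroid comparison is normally read as a measure of steroid sparing: the better drug lets patients come off prednisolone sooner. The article states no rule by which a better response lowers the dose, and it prefers a fixed schedule to symptom-triggered dosing. A patient on schedule takes the same prednisolone in either arm.

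Two things follow. Most of the measured quantity is scheduled dose, which carries no information about azathioprine versus MMF and only widens the interval around whatever off-schedule use occurs. And a cumulative total depends on how long it is counted. If counting stops at study withdrawal, and withdrawal on stopping the drug is written into one arm only, the shorter count could be mistaken for steroid sparing.

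**Working it through.** The article states no expected cumulative dose, so there is no figure of its own to reproduce. The totals below are built from Tables 2 and 3.

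**Inputs**
- Weeks 1–4, mg/day: 40, 30, 25, 20 (40–80 kg); 60, 45, 30, 20 (>80 kg).
- Both bands: 15 in week 5, 12.5 in week 6, 7.5 in weeks 9–10, 5 from week 11.
- Weeks 7–8: not legible in the text at hand. Assumed 10 mg/day in both bands; range 7.5–12.5 from the neighbouring rows.
- 35 patients per arm (Sample size calculation).
- Share over 80 kg: not given; assumed 40%.
- Azathioprine cessation: about 15% in the first year (Background).

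**1. Scheduled totals**
- Weeks 1–4: 7 × (40+30+25+20) = 805 mg; 7 × (60+45+30+20) = 1,085 mg.
- Weeks 5–24: 7×15 + 7×12.5 + 14×10 + 14×7.5 + 98×5 = 927.5 mg.
- Totals: 1,732.5 mg and 2,012.5 mg. The weeks 7–8 range moves each by ±35 mg.
- Given before either study drug: 805/1,732.5 = 46%; 1,085/2,012.5 = 54%.
- Scheduled difference between arms within a band: 0 mg. Between bands: 280 mg.

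**2. Noise from weight mix**
- Variance at 40% over 80 kg: 280² × 0.4 × 0.6 = 18,816, so SD = 137 mg.
- SE of the arm difference: 137 × √(2/35) = 33 mg (27 mg if 20% are over 80 kg, 33 mg if 50%).

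**3. What that noise costs (assumed illustration)**

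Suppose 20% of one arm take 5 mg/day extra for 16 weeks.
- Extra per such patient: 5 × 112 = 560 mg. Shift in the arm mean: 0.2 × 560 = 112 mg. Added variance: 560² × 0.2 × 0.8 = 50,176.
- Raw total: SE = √((2×18,816 + 50,176)/35) = 50 mg, so the shift is 2.2 SE.
- Taken minus scheduled: SE = √(50,176/35) = 38 mg, so the shift is 3.0 SE.

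**4. Possible truncation**
- Dose lost if counting stops after week 8: 14×7.5 + 98×5 = 595 mg. After week 12: 420 mg; week 16: 280 mg; week 20: 140 mg. Averaged over stopping times spread evenly across weeks 5–24: about 375 mg.
- Rates: 15%, or 1 − 0.85^(20/52) = 6% if first-year cessation is spread over the year and only the 20 drug weeks count.
- Assume nobody in the MMF arm is cut short.

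| Azathioprine patients cut short | Fall in mean | SE | Ratio |
|---|---|---|---|
| 6%, spread over weeks 5–24 | 0.06 × 375 = 22.5 mg | 37 mg | 0.6 |
| 6%, all after week 8 | 0.06 × 595 = 36 mg | 41 mg | 0.9 |
| 15%, all after week 8 | 0.15 × 595 = 89 mg | 49 mg | 1.8 |

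For week 8 stops, the SE adds 595² × p(1−p) to the variance of one arm; for example, √((2×18,816 + 45,138)/35) = 49 mg. For spread stops the mean squared loss is about 198,400, so the added variance is 0.06 × 198,400 − 22.5² = 11,398, and √((37,632 + 11,398)/35) = 37 mg.

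**The case against.** The strongest defence is randomisation. Weight band and the weeks 1–4 dose have the same expectation in both arms, so they add variance, not bias, and the standard error covers them. With complete follow-up, the raw difference already estimates off-schedule steroid use. The article leaves room for such use: reaching 5 mg daily is worded as an aim, and drug stoppers move to standard of care. All of this stands. A reader might infer that the outcome is void, or that a real excess of steroid use would be hidden. The documents do not support that: in step 3 the excess is still 2.2 SE on the raw total.

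A second defence is that the article fixes no counting window or treatment of early leavers, and that such details belong in an analysis plan that is not shown. This stands as far as omission goes. The point here rests on what is stated: an identical fixed schedule, different follow-up wording by arm, and an intention-to-treat rule tied to study discontinuation.

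Third, a reader might infer that azathioprine failure will look like steroid sparing. That goes too far. The withdrawal section provides for observational recording and for a visit four weeks after withdrawal that includes concomitant medication, so truncation is possible but not established. The azathioprine withdrawal rule concerns persisting adverse events, not lack of response. The upper end in step 4 puts a full year's cessation at week 8 in one arm only, and even that stays below 2 SE.

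Finally, the efficacy lead-in is loose, since the same list holds adverse events and survival. Little weight should rest on that label.

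**Conclusion.** The point holds in a limited form. The cumulative corticosteroid difference is weakly informative as stated, because the schedule contributes 0 mg between arms within a weight band and about half of it precedes either study drug. The 280 mg band gap costs precision (SE about 33 mg, assuming 40% over 80 kg and weeks 7–8 at 10 mg/day in both bands).

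A downward bias in the azathioprine total is possible because of the follow-up wording. Its illustrative size is about 20–90 mg, or 0.6–1.8 SE. This depends entirely on the assumed rate, timing and one-sidedness of truncation, and it vanishes if dosing after withdrawal is counted in both arms.

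That the raw total mainly reflects weight and time in study is a further reading the documents do not settle, because the amount of off-schedule use is unknown. The primary outcome and sample size are unaffected.

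**What to change.** - Define the tested quantity as corticosteroid taken minus the dose scheduled for the patient's own weight band, from first study-drug dose to week 24, in all intention-to-treat patients. Adjusting the total for weight band is an acceptable alternative.
- Count the observational data after withdrawal in both arms instead of stopping at withdrawal. Dividing by weeks observed is no substitute, because it would still drop steroid use after withdrawal.
- Report the percentage in each arm who left the schedule, and keep the raw cumulative total as description.
- Reconcile the withdrawal section and the two treatment-group sections on follow-up after a study drug is stopped, so that it is clear whose data are recorded to week 24 and used.

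Cost: one outcome definition and a small derivation from dosing and concomitant-medication records. Weight is already needed for dosing, and no patients are added. The raw total is no longer the tested quantity. Where no records exist after withdrawal, the gap remains and should be reported by arm.
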